**Results:**

It is expected that the repetition rate in the intervention group will decline after implementing the intervention and the change will be statistically significant (*P*<.05). Furthermore, it is expected that the knowledge, motivation, and skill levels in the intervention group will increase significantly among radiographers after implementation of the intervention (*P*<.05). Meanwhile, knowledge, motivation, and skills in the control group will not change.

**Conclusions:**

A quasi-experimental time series with a control will be conducted to investigate the effect of printed educational material in reducing the repetition rate of routine digital chest radiographs among radiographers in tertiary hospitals in the Makkah Region of Saudi Arabia.

## Introduction

Good quality images in routine radiography should provide an adequate picture of the body’s anatomy. Failure to obtain a good quality image requires the radiograph to be repeated. According to Foos et al [1], the term “repetition” refers to redoing a radiograph of a patient that was deemed clinically unacceptable. Repetition of an image is a critical event in radiology. It is recommended that the repetition rate should not exceed 5% [2-7]. The Diagnostic Imaging Quality Assurance Committee recommends that the repetition of radiographs should not exceed 5% to 7% [8]. The American Association of Physicists in Medicine recommends keeping the repetition rate below 6%, and when it increases to 10%, corrective action should be conducted [9]. The Australian College of Radiologists recommends an acceptable repetition rate of 2% and not more than 5% [10].

A study by Khafaji and Hagi [11] reported high repetition rates of radiography in Saudi hospitals, averaging 14.9%, which is higher than the international standard. Another study reported the repetition rate in 3 Ministry of Health hospitals ranged from 7.4% to 9.7%. The same study revealed that chest radiographs have higher repetition rates compared to other radiological procedures [12]. Related to that, it was revealed that radiographer error is one of the factors that strongly contribute to the issue of the repetition [13,14].

The production of high-quality images is based on radiographer practices. According to the World Health Organization, practice is influenced by the level of knowledge, motivation, and skills [15]. A study conducted in Saudi Arabia by Alsharif et al [16] showed that there is poor knowledge among radiographers in identifying image error. Another study conducted in Saudi Arabia by Ahmed et al [17] revealed that there is variation in radiographer knowledge of radiation protection, with 58% of radiographers indicating poor knowledge. Additionally, it was revealed that the motivation level of radiographers is low and this affects production of high-quality images [18]. Lack of knowledge and motivation dramatically influence skill level. It has been exhibited that the increase in repetition rate is due to deficiencies in radiographer skills [19]. Radiographers with high skills tend to avoid errors in the imaging process. Skills include the ability to communicate properly with the patient and handling the equipment accurately.

Repeated radiographs have financial and health implications, especially because of increased exposure to radiation for both staff and patients [12]. Khafaji and Hagi [11] and Khoshinani and Heidari [20] added that a high repetition rate in radiography consumes the digital equipment’s lifetime by 2 months each year. This increases both staff workload and waiting time for the patient in addition to affecting the achievement of the organization’s vision.

According to Almalki et al [21], most interventions conducted in previous studies are technical in nature. Despite that, those intervention studies show a positive impact on the repetition rate of digital radiography. However, radiographers were not included in the studies despite them being significant factors in the repetition rate.

In general, the aim of this study is to develop, implement, and evaluate the impact of printed educational material in reducing the repetition rate of routine digital chest radiography among radiographers in Makkah Region tertiary hospitals.

## Methods

### Study Design

The design of this study is basically a quasi-experimental time series with a control group. This design was chosen because the intervention was recommended by other researchers [22,23]. A quasi-experimental study is the only design that could be applied in this study. The difficulty of randomizing by location and subject and the small number of the population make the quasi-experimental design suitable in this study [24]. In addition, there is difficulty in randomizing by subject to avoid potential contamination. Location is also a factor, since no 2 hospitals are similar.

The Makkah Region of Saudi Arabia was selected for the study because the problem has been ignored in the area and the repetition rate has not been periodically measured there [25,26]. Out of 5 hospitals, 4 will be selected to be in the study since randomization is not required in this type of study [27]. The hospitals involved are under the direction of Makkah Region health affairs. Two will be chosen as an intervention group and 2 as a control group. Preintervention assessment will be conducted in both groups at the same time during the second quarter of 2017. The intervention will be distributed to radiographers in the intervention group, and after 1 month, an assessment will be conducted. Six months after the implementation of intervention, a second postintervention assessment will be conducted. Figure 1 demonstrates the study flow.

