**Methods:**

A quasi-experimental time series with a control group will be conducted in Makkah Region tertiary hospitals for 8 months starting in the second quarter of 2017. Four hospitals out of 5 in the region will be selected; 2 of them will be selected as the control group and the other 2 as the intervention group. Stratification and a simple random sampling technique will be used to sample 56 radiographers in each group. Pre- and postintervention assessments will be conducted to determine the radiographer knowledge, motivation, and skills and repetition rate of chest radiographs. Radiographs of the chest performed by sampled radiographers in the selected hospitals will be collected for 2 weeks before and after the intervention. A piloted questionnaire will be distributed and collected by a researcher in both groups. One-way multivariate analysis of variance and 2-way repeated multivariate analysis of variance will be used to analyze the data.

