#### Matching

Matching has been used in research since the beginning of the 19th century [28]. Exact matching is the method that will be employed in this study. Stuart and Rubin [29] recommended the selection of the most common covariate that has an effect on the outcome in order to make matching possible. According to Loman [30], exact matching can be employed for up to 5 variables. Based on these principles, variables that underwent matching include gender, experience, education level, training, and the type of university from which a radiographer graduated.

Respondent characteristics will be obtained from the radiographers in charge in the control group. First, a sample from the intervention group will be randomly selected using a software number generator. Since the list of radiographers in the control group and the characteristics have already been obtained, exact matching can be performed. This method will help in making the groups comparable and similar in terms of confounder distribution.

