### Limitations

There are some limitations to this study beginning with the research design. The threat of internal validity mostly reduces the inference of causality due to the lack of randomization. However, the researcher will make the groups comparable and similar by using the exact matching technique. Another limitation is that the result cannot be generalized to all of the hospitals in the Makkah Region due to differences in hospital equipment, which may be conventional, computed, or direct forms of radiography. These modalities are totally different than the others, but the result can be generalized on tertiary hospitals in the region.

The printed education intervention could serve as a new modality to manage the critical event of repetition among radiographers. The study aims to provide better recognition and management of the repetition rate of routine digital radiography through increasing knowledge, motivation, and skills. It also aims to educate and create awareness of the problem of repetition in radiography. There is a need to develop simple, brief, and effective interventions tailored to the needs of the radiology department to reduce the burden of repetition among radiographers.

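### No rule is stated for which two of the four hospitals receive the module, and the reasons given do not rule out a random draw

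*Protocol article*

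**What the plan says.** The Study Design section selects the sites first: "Out of 5 hospitals, 4 will be selected to be in the study since randomization is not required in this type of study". The remark about randomization is attached to taking four of the five hospitals. The assignment to arms follows as a separate statement: "Two will be chosen as an intervention group and 2 as a control group". The abstract is no more specific: "2 of them will be selected as the control group and the other 2 as the intervention group". Neither place says how, or by whom, the arms are settled.

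The same section gives its grounds for a quasi-experimental design, which it regards as the sole feasible one:
- "The difficulty of randomizing by location and subject and the small number of the population make the quasi-experimental design suitable in this study"
- "there is difficulty in randomizing by subject to avoid potential contamination"
- "Location is also a factor, since no 2 hospitals are similar"

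Under Sampling Methods and Matching, random number software is used only to sample radiographers. Comparability of the arms is to come from exact matching: "variables that underwent matching include gender, experience, education level, training, and the type of university from which a radiographer graduated". The Limitations section concedes that "The threat of internal validity mostly reduces the inference of causality due to the lack of randomization", and then relies on that matching to make the groups comparable.

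**The concern.** Whole hospitals are assigned to arms, so the assignment of four units is the central step of the comparison. If it is made by discretion, the module can be confounded with whatever led to a hospital being picked. Examples are a more cooperative department, different equipment, or a high repetition rate that would tend to fall on remeasurement anyway. This is the threat to causal inference that the Limitations section itself names.

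The issue is more than a detail left to a fuller document. The article argues positively that randomization is not feasible, and that argument can be tested against its own text. If it fails at hospital level, the trial accepts an avoidable source of bias.

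**Working it through.** **1. Do the stated reasons exclude a hospital-level draw?**
- *Contamination.* The article raises it against randomizing individuals. It favours allocating whole hospitals, which the plan already does, and is no argument against drawing those hospitals at random.
- *Dissimilar hospitals.* Differences between sites make discretionary assignment more hazardous. They limit the balance that a draw can achieve but do not prevent a draw.
- *Small population.* Two of four hospitals can be drawn whatever the number of radiographers.
- *Difficulty by location.* This is the only reason that bears directly on a hospital-level draw, and no concrete obstacle is named.
- *Randomization not being required in this type of study.* This explains taking four of five sites. As a reason for not randomizing the arms it would be circular, because the lack of randomization is what defines the design type.

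**2. Is a draw practicable on the article's own facts?** The intervention is printed material (Intervention section). The hospitals under study have given approval (Ethics Approval and Registration). A number generator is already planned for radiographers. The intervention sample is drawn first and controls are then matched to it (Matching), so a hospital draw need only come before that step. No material cost is evident.

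**3. Does matching substitute for it?** The five matching variables are gender, experience, education level, training and type of university. All describe the radiographer. None describes the hospital, such as its equipment, workload or baseline repetition rate.

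**4. What would a draw achieve?** The plan states no figure on this point to reproduce, and the sample sizes do not change.
- Number of allocations of 4 hospitals to 2 versus 2: C(4,2) = 6.
- Smallest one-sided randomization p-value: 1/6 = 0.167.
- Smallest two-sided value, counting the mirror-image allocation: 2/6 = 0.333.

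**5. How large could a baseline gap between arms be? (Illustration only.)** The Introduction cites 7.4% to 9.7% across three hospitals in another study, a spread of 9.7 − 7.4 = 2.3 points. The Sample Size section plans on 8.7% versus 5.84%, a difference of 2.86 points. The rates of the four trial hospitals are not given, so two sets are assumed within the cited range:

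| Assumed rates (%) | Gaps between arm means over the 6 allocations (absolute, points) |
|---|---|
| 7.4, 7.4, 9.7, 9.7 | 2.3 in two allocations, 0 in four |
| 7.4, 8.2, 8.9, 9.7 | 1.5 in two, 0.8 in two, 0 in two |

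The largest gaps are (9.7 + 9.7)/2 − (7.4 + 7.4)/2 = 2.3 in the first row and (8.9 + 9.7)/2 − (7.4 + 8.2)/2 = 1.5 in the second. As shares of the planned difference these are 2.3/2.86 = 0.80 and 1.5/2.86 = 0.52. A random draw can still land on the worst allocation.

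**The case against.** The design is declared openly in the title, the Study Design section and the Limitations section, so nothing is hidden or contradictory. The article is condensed and its flow figure is not shown, so the rule may exist elsewhere. The wording is passive. A reader might infer that the investigators hand-pick the intervention hospitals, but the article names no agent and does not say so. All of this stands. It does not rescue the argument that randomization is infeasible, which the article makes in its own words.

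The analysis also offers protection. Both arms have a concurrent baseline and two later assessments, at one and six months, with repeated-measures methods. A stable difference in level between hospitals is not an effect in a group-by-time comparison. That stands too. What baseline measurement does not remove is a difference in drift between hospitals, or regression to the mean if high-rate hospitals were picked.

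A reader might infer from the Introduction that the 2.3-point spread between hospitals could by itself produce a difference of the planned 2.86 points. The documents do not support this. The range comes from three hospitals in another study and appears to cover all procedures, not chest radiographs alone. It compares single hospitals, whereas each arm averages two. Within that range the gap between arms never exceeds 2.3 points, and the article gives no figure for differential drift.

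Finally, a draw may have a cost: some pairs of control hospitals might not supply 56 exact matches on five variables. The article does not say that matching drives the assignment. If it does, that is a concrete obstacle and should be stated.

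**Conclusion.** The point holds as a weakly justified design choice that should be changed; it is not an error or a contradiction. The article gives no rule for assigning four hospitals to two arms, its reasons do not exclude a hospital-level draw, and radiographer matching cannot correct hospital-level selection. The size of any bias cannot be estimated from the article, because neither the trial hospitals' rates nor their likely drift is given.

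The benefit of a draw is limited. It removes bias from deliberate choice only. With six allocations and a smallest two-sided randomization p-value of 0.33, chance imbalance and confounding of arm with hospital remain.

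Two further inferences go too far. One is that the four hospitals should themselves be drawn from the five. That choice does not decide which arm a participating hospital joins, and approvals are recorded only for the hospitals under study. The other is that adding hospital to the model would solve the problem. Hospital is nested in arm with two per arm, so only 4 − 2 = 2 degrees of freedom for variation between hospitals within arms are available.

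The conclusion assumes that no undisclosed obstacle prevents a draw and that the module can be delivered at any of the four sites.

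**What to change.** In Study Design, replace "Two will be chosen as an intervention group and 2 as a control group" with a statement that two of the four participating hospitals will be drawn at random to receive the module. The draw would use the number generator already planned and be made before radiographers are sampled and matched. Change the abstract to agree. If a concrete obstacle prevents the draw, state that obstacle and the assignment rule actually used.

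In Limitations, add that the draw removes only bias from deliberate choice, that 2 versus 2 hospitals leaves chance imbalance and confounding of arm with hospital, and that the conclusion will therefore rest on change from baseline and be worded cautiously.

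The cost is small: the team loses its choice of site, and the radiographer lists are needed from whichever hospitals become controls. Sample size, intervention and schedule are unaffected.

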**Figure 1 figure1:**
[figure not shown]
Study flow.

### Selection Criteria

The inclusion and exclusion criteria are based on the job description of a radiographer, since there are several tasks in routine radiography in the radiology department. Only radiographers who perform routine digital chest radiography will be included. Clerk radiographers, administrative radiographers of routine digital radiography, radiographers who are on long annual leave, and radiographers who are pregnant will be excluded. Non-Saudi radiographers will be excluded as well.

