### Sample Size

We will use the formula by Lemeshow et al [31] to estimate the minimum sample size required in intervention studies and to test a hypothesis of proportion of 2 population problems in terms of the radiographers sample size (see Figure 2), where *p* 1 and *p* 2 were obtained from a study by Moreira [32] to estimate the sample size of radiographers in each group and Z1–α=1.96, Z1–β=0.842, *p* 1 is 0.63, *p* 2 is 0.88, and *p*^–^=0.755. Figure 3 displays the sample size estimation of the secondary outcome variables.

According to Sullivan [33], the attrition rate (dropout) can be calculated by the formula (desired sample size)/(percent retained). Hence, for this study, a sample size of 56 for each group was targeted.

In terms of the repetition rate of routine digital chest radiographs sample size, the same formula was used, where *p* 1 and *p* 1 were obtained from the study of Zhang and Chu [34] to estimate the sample size of routine digital chest radiography in each group and Z1–α=1.96, Z1–β=0.842, *p* 1 is 0.0584, *p* 2 is 0.087, and *p*^–^=0.0728. Figure 4 displays the sample size estimation of the primary outcome variable.

According to Sullivan [33], the attrition rate that may occur due to any loss of chest images can be calculated by the formula (desired sample size)/(percent retained). The sample size of routine digital chest radiographs is 1618 for each group, and this number is expected to be reached within 2 weeks. Two weeks’ time is similar to that used in the study conducted by Ahmed and Suliman [35].

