## Discussion

### Summary

This quasi-experimental time series with control group aims to investigate the effect of printed educational material on radiographer knowledge, motivation, and skills and the radiography repetition rate.

Educating radiographers helps reduce the dose of radiation exposure on patients, decreases waiting time, and increases patient satisfaction. A reduction in the repetition rate decreases the dose of radiation and reduces the workload. This intervention is significant to the organization as it reduces the burden of equipment consumption and cost as well as assists the organization in achieving its vision and goals. In addition, implementing an educational program that focuses on reducing the repetition rate of radiographs has been highly recommended [12,40,41].

To our knowledge, this is the first study that combines 4 outcome variables—knowledge, motivation, skills, and the repetition rate of routine digital chest radiography—and aims to investigate the effect of using printed educational material on the repetition rate of routine digital chest radiography. Furthermore and based on our knowledge, this is the first study that analyzes the repetition rate among radiographers.

The intervention module will be made available in both English and Arabic languages, and participants can choose their preferred language to complete the sessions. The intervention program was designed to be as brief as possible to increase readability. The printed educational material was selected because of the difficulty of assembling radiographers from different cities in one place at one time. There is a need to overcome the issue of bias to increase the credibility of the study. The quasi-experimental design is one of the strongest designs for this particular research.

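### The repetition rate is sized on films, but the named repeated-measures MANOVA weights every radiographer equally whatever the film count; model repeats out of films instead

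*Protocol article*

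**What the plan says.** Selection Criteria: "Only radiographers who perform routine digital chest radiography will be included". Some staff who would produce few films are removed: "Clerk radiographers, administrative radiographers of routine digital radiography, radiographers who are on long annual leave, and radiographers who are pregnant will be excluded". Non-Saudi radiographers are excluded too. No number of films is required.

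Abstract, Methods: "Radiographs of the chest performed by sampled radiographers in the selected hospitals will be collected for 2 weeks before and after the intervention". Study Design sets three assessments: before the intervention, 1 month after it and 6 months after it.

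Sample Size: for radiographers, "a sample size of 56 for each group was targeted"; for films, "The sample size of routine digital chest radiographs is 1618 for each group, and this number is expected to be reached within 2 weeks". The film figure rests on repetition rates of 5.84% and 8.7%.

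Instruments: the check list records, for each radiographer, the films performed and the films repeated.

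Statistical Analysis names chi-square, one-way MANOVA, two-way repeated-measures MANOVA, MANCOVA and the Cochran Q test. It mentions no weighting. The primary outcome section does not say whether the rate belongs to a film, a radiographer or a group. The Discussion treats the rate as one of four outcome variables beside knowledge, motivation and skills, and says "this is the first study that analyzes the repetition rate among radiographers".

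**The concern.** The sample size counts every film once. A repeated-measures MANOVA needs the same unit at each assessment. A film exists in one window only, so the recurring unit is the radiographer, and the outcome becomes one percentage per person per window. MANOVA then treats a percentage from 5 films as being as informative as one from 80.

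Two things are at stake. The first is precision: the information in 1618 films is fully used only if volumes are similar, and nothing in the plan makes them so. The second is completeness: a radiographer with no films in one window has no rate there and is lost from a complete-case repeated analysis, including the windows in which that person did contribute.

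**Working it through.** **Inputs.** From Sample Size: p1 = 0.0584, p2 = 0.087, mean 0.0728, Z values 1.96 and 0.842, 1618 films and 56 radiographers per group. Assumed here: 20% loss (the text gives no percentage), gamma-Poisson film volumes with the CVs shown, and the between-radiographer SD.

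**1. The plan's own figure.** The formula figure is not shown, so I used the usual two-proportion form:

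n = [1.96·√(2·0.0728·0.9272) + 0.842·√(0.0584·0.9416 + 0.087·0.913)]² / 0.0286² = (0.7202 + 0.3087)² / 0.000818 ≈ 1294.

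1294.1/0.80 = 1617.7, so 1618 is reproduced. The same form with 0.63 and 0.88 gives 45.3 radiographers, and 45/0.80 = 56.25, in line with 56. The film figure treats films as independent units.

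**2. Films per radiographer.** 1618/56 = 28.9 per window if the minimum is just met. Expected repeats are 28.9 × 0.0584 = 1.7 and 28.9 × 0.087 = 2.5.

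**3. Precision of one rate.** At 8.7%, SE = √(0.087 × 0.913/n): 5.2 points at 29 films, 8.9 at 10 and 12.6 at 5. The chance of observing 0% is 7%, 40% and 63% respectively. Low-volume rates are therefore much noisier, and a rate is undefined only at zero films.

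**4. Cost of equal weights, sampling variance only.** For k radiographers with n_i films each and N films in all:

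- equal weights: variance = p(1−p) × mean(1/n_i)/k
- film weights: variance = p(1−p)/N
- ratio = mean(1/n_i) × mean(n_i)

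Simulated with mean 28.9, 56 radiographers, and zero-film radiographers dropped:

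| Assumed volume CV | Variance ratio | Effective films | Power, 5.84% vs 8.7% | Zero films in a window |
|---|---|---|---|---|
| about 0 | 1.04 | 1560 | 87% | 0% |
| 0.5 | 1.4 | 1126 | 74% | 0.02% |
| 0.8 | 2.5 | 644 | 51% | 1.0% |
| 1.0 | 3.5 | 456 | 38% | 3.3% |

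Pooling or weighting by films gives 88% power on 1618 films at any CV. All these powers ignore clustering by radiographer and hospital, so they serve only to compare the two weightings.

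**5. Allowing true rates to differ.** With between-radiographer SD s, put q = p(1−p) − s². Then:

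- equal weights: [s² + q × mean(1/n_i)]/k
- film weights: s² × Σn_i²/N² + q/N

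At p = 0.087, s = 0.05 and CV 0.5, q = 0.0794 − 0.0025 = 0.0769 and q/28.9 = 0.00266. Multiplied by k:

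- equal weights: 0.0025 + 1.43 × 0.00266 = 0.0063
- film weights: 0.0025 × (1 + 0.25 + 1/28.9) + 0.00266 = 0.0059

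The ratio is about 1.1. Simulation gives 1.08 at CV 0.5 and 1.55 at CV 1.0, that is about 1.1 and 1.6. At p = 0.0584 with the same SD the ratios are 1.0 and 1.3. At p = 0.087 with an SD of 10 points they are 0.89 and 0.84, so equal weighting is then the better of the two simple choices.

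**6. Drop-out from the repeated analysis.** At CV 1.0, 3.3% have no films in a given window. If the three windows were independent, 1 − (1 − 0.033)³ = 9.6%, or about 5 of 56, would lack at least one rate. At CV 0.8 the figure is 1 − (1 − 0.0096)³ = 2.9%, or between 1 and 2 of 56. At CV 0.5 it is negligible.

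**The case against.** The document never states that the primary comparison uses unweighted radiographer rates. The primary outcome names no unit, the sample size is in films, chi-square could be run on films, and the remark about analysing the rate among radiographers is a claim of novelty. Weighting is also a detail that an article may leave to a fuller plan. This stands in part: the unit is inferred. But the article does name the repeated-measures method, and that method can only follow radiographers. Cochran Q likewise needs the same units on each occasion. Equal weighting comes with the named method, so this is a choice the text makes and not a detail it leaves out.

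No volume distribution is given, and the exclusion of clerk, administrative and long-leave staff makes very low volumes less likely. That stands, so every multiplier is conditional on an assumed CV. The 1618 is a minimum already inflated for loss, so 29 films is not a projected workload. That stands too.

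A reader might infer more: that low-volume radiographers make the primary outcome meaningless or biased, and that eligibility needs a minimum volume or each person a fixed quota of films. The document does not support this. Noise in individual rates does not bias a comparison of group means unless volume differs between groups or is related to the rate, and neither is shown. A quota of 29 films yields 56 × 29 = 1624, only 6 above target, and discards films from busy staff. If, say, half the staff took 8 films in 2 weeks and half took 50, a 29-film quota with a 4-week cap would yield 28 × 16 + 28 × 29 = 1260. A volume floor would also shrink a pool that the protocol calls small and that must support exact matching on five variables.

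**Conclusion.** The point holds as a mismatch between how the primary outcome is sized and how it is to be analysed. Eligibility and the 2-week window are not errors. Under the named repeated-measures MANOVA, the sampling part of the variance of a group's mean rate would be about 1.4 times (CV 0.5) to 3.5 times (CV 1.0) that of a film-weighted analysis. The total penalty is about 1.1 to 1.6 times if true rates vary with an SD of 5 points around 8.7%, and can reverse if they vary much more. Complete-case handling would also lose anyone with an empty window. The harm is to precision; no bias is demonstrated. The conclusion rests on an assumed volume spread and on reading the radiographer as the repeated unit. It is worth correcting because the counts needed are already collected.

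**What to change.** Leave Selection Criteria and the 2-week window as they are. In Statistical Analysis, and in the matching sentence of the Abstract, state that the repetition rate will be analysed from each radiographer's repeats out of films at each assessment. Use a binomial (logistic) mixed model or GEE with group, time and group-by-time, and clustering by radiographer. A simpler alternative is a regression of rates weighted by films. Keep MANOVA for knowledge, motivation and skills. A radiographer with no films in one window then still contributes in the others.

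The cost is wording and analysis work, with no new data. The small downsides are that the repetition rate leaves the joint MANOVA, and that simple film weighting can lose some efficiency if radiographers differ very widely (about 1.1 to 1.2 times the variance of equal weighting at an SD of 10 points: 1/0.89 and 1/0.84). The mixed model avoids the second, because it weighs both sources of variation.
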